## Abstract

**Background:**

Compassion-based interventions delivered over the internet are showing promising results for the promotion of psychological health and well-being. Several studies have highlighted their feasibility, acceptance, and preliminary efficacy. However, this is an incipient field of research, and to the best of our knowledge, there are no data available from Spanish-speaking countries.

**Objective:**

The aim of this study is to investigate the feasibility, acceptance, and preliminary efficacy of the Internet Attachment–Based Compassion Therapy (iABCT), a web-based version of the Attachment-Based Compassion Therapy, in Spanish speakers from the general population.

**Methods:**

This feasibility study features a single-arm, uncontrolled, within-group design with an embedded qualitative and quantitative process evaluation at baseline, immediately after the intervention and at the 3-month follow-up. A minimum of 35 participants from the general population will be allocated to iABCT. Feasibility measures will include attrition rate, patterns of use of the web-based system, and participants’ acceptability, usability, and opinion. The primary outcome was measured using the Pemberton Happiness Index. Secondary outcomes were measured using the Compassion Scale, Self-Compassion Scale, Forms of Self-Criticizing/Attacking and Self-Reassuring Scale-Short form, Five Facets of Mindfulness Questionnaire, Relationships Questionnaire, General Health Questionnaire, Non-Attachment Scale, International Positive and Negative Affect Schedule Short Form, Purpose-In-Life Test, and difficulties regarding the practice of compassion (Compassion Practice Quality Questionnaire). Mixed models will be used to evaluate primary and secondary outcome measures. A qualitative content analysis of the participants’ qualitative responses will also be performed.

**Results:**

Enrollment started in February 2020 and will be finished in April 2020. Data analysis will start in October 2020.

**Conclusions:**

To our knowledge, this study will, for the first time, show data on the feasibility, acceptability, and preliminary efficacy of web-based compassion (and self-compassion) training—that is, the adapted iABCT—in Spanish speakers from the general population. Further aspects of their implementation (ie, facilitators, barriers, and unwanted effects) and mechanisms of change will be investigated. This study will allow the revision and fine-tuning of the developed intervention, study design, and planning procedures, as well as the initiation of a future randomized controlled trial.

**Trial Registration:**

Clinicaltrials.gov: NCT03918746. Registered on April 17, 2019. Protocol version 1, 6 March 2019.

**International Registered Report Identifier (IRRID):**

PRR1-10.2196/16717

## Introduction

### Compassion-Based Interventions

Compassion-based interventions (CBIs) focusing on cultivating compassion and self-compassion have recently been developed with promising results for the general population as well as for the treatment of a number of different psychological disorders [1-5]. In particular, *self-compassion*, which involves the directing of compassion toward oneself, is emerging as a strong predictor of well-being, psychological health, and quality of life [6-10]. A recent meta-analysis study of randomized controlled trials (RCTs), for the clinical and nonclinical population, showed significant between-group differences with moderate effect sizes with regard to cultivating compassion (*d*=0.55; *k* [number of studies]=4; 95% CI 0.33-0.78), self-compassion (*d*=0.70; *k*=13; 95% CI 0.59-0.87), and mindfulness (*d*=0.54; *k*=6; 95% CI 0.38-0.71), reducing depression (*d*=0.64; *k*=9; 95% CI 0.45-0.82), anxiety (*d*=0.49; *k*=9; 95% CI 0.30-0.68), and psychological stress (*d*=0.47; *k*=14; 95% CI 0.19-0.56) and improving satisfaction with life and well-being (*d*=0.51; *k*=8; 95% CI 0.30-0.63), which remained when active control comparisons were included [4]. Kirby [3] found 8 face-to-face established CBIs with 6 of them having RCTs and meta-analysis evidence [4]. Those 6 CBIs were Compassion-Focused Therapy [11], Mindful Self-Compassion [12,13], Compassion Cultivation Training [14,15], Cognitively Based Compassion Training [16-18], Cultivating Emotional Balance [19,20], and Compassion and Loving-Kindness Meditations [21,22]. The other 2 CBIs pending the publication of evidence were the ReSource Training Protocol [23] and the Being with Dying Programme [24]. Another systematic review and meta-analysis investigated the effectiveness of self-compassion–related therapies (ie, CBIs, mindfulness-based cognitive therapy, and acceptance and commitment therapy). It found greater improvements in promoting self-compassion (g=0.52; 95% CI 0.32-0.71) and in reducing psychopathology (depression: g=0.40, 95% CI 0.23-0.57; anxiety: g=0.46, 95% CI 0.25-0.66) in clinical and subclinical populations, although the results did not remain when analyses were restricted to the comparison between self-compassion–related therapies and active control conditions [2].

### Attachment-Based Compassion Therapy

To the best of our knowledge, the attachment-based compassion therapy (ABCT) program is the first CBI to have been originally developed and validated in the Spanish language [6]. To date, ABCT—in the face-to-face group format, specifically—has shown its efficacy and applicability in a nonrandomized controlled study of healthy people (ie, adults not having a psychological disorder and not receiving any psychiatric treatment) [1] and in an RCT for the treatment of fibromyalgia [5]. In a study on the general population, Navarro-Gil et al [1] found significant improvements in self-reported measures of self-compassion, dispositional mindfulness, and secure attachment style, as well as significant reductions in psychological disturbance, experiential avoidance, and levels of anxiety and avoidance toward social relationships as compared with the waiting list control group. Moreover, the authors pointed out that the significant increments in secure attachment style in the ABCT group were mediated by changes in self-compassion. The results of the RCT on patients with fibromyalgia revealed greater improvements in general health status, clinical severity, anxiety, depression, quality of life, and psychological flexibility in the ABCT group (combined with treatment as usual [TAU]) compared with an active control group (relaxation combined with TAU) at postintervention and 3-month follow-up. An interesting finding was that the effect sizes found were larger than those obtained when treating fibromyalgia using cognitive behavioral therapy (CBT) or mindfulness-based interventions (MBIs). Moreover, psychological flexibility partially mediated the relationships between the experimental condition (ABCT and TAU vs relaxation and TAU) and overall health status, pain catastrophizing, anxiety, and depression at follow-up. Nevertheless, these studies did not include any specific well-being outcomes, indicating that further research is needed in this regard.

### Internet-Delivered Compassion-Based Interventions

There are promising results that suggest the potential utilities of web-based compassion training. One of the first studies is the research conducted by Krieger et al [25], testing the feasibility of a web-based version of the Mindfulness-Based Compassionate Living program in self-referred participants suffering from harsh self-criticism (N=39). Authors found high levels of satisfaction with the program; significant increases in self-compassion, mindfulness, reassuring self, and satisfaction with life; and significant reductions in inadequate self, hated self, perceived stress, and fear of self-compassion from pretreatment to posttreatment and from posttreatment to follow-up at 6 weeks, with medium-to-large within-effect sizes (*d*=0.50-1.50). A replicated RCT in 122 participants supported the preliminary evidence, including the maintenance of the effects at 6-month follow-up. The dropout rate was 11.6%. Other adherence outcomes (ie, number of completed modules and self-reported number of completed exercises per week) predicted postintervention scores for self-compassion but not for depressive, anxiety, and distress symptoms in the intervention group.

Finlay-Jones et al [26] gathered preliminary data on the feasibility and effectiveness of the Internet-Based Self-Compassion Cultivation Program for Psychology Trainees (N=37) in a pilot study. After completing the 6-module program, participants reported significant changes in self-compassion, happiness, depression, perceived stress, and emotion regulation difficulties at postintervention and 3-month follow-up. Program feedback from participants revealed high average levels across modules for enjoyableness, relevance, comprehension, and learning and low-to-moderate average levels for difficulty. Recently, Eriksson et al [8] pointed out the effects of a brief web-based mindful self-compassion program on stress and burnout symptoms in a group of practicing psychologists (N=81) and the relationships between changes in self-compassion and self-coldness and changes in stress and burnout symptoms in an RCT. After the 6-week training (15 min per day of an online exercise), the results showed significant increases in self-reported self-compassion and reduced burnout symptoms, perceived stress (*d*=0.59), and self-coldness levels. Measures of distress were strongly related to self-coldness rather than self-compassion.

In summary, there is incipient evidence that supports the feasibility, acceptance, and preliminary effectiveness of CBIs delivered over the internet. However, to our knowledge, the existing research has mostly been conducted in English-speaking countries. Data regarding how Spanish speakers would accept CBIs are needed to determine the feasibility to apply it in this population, to cover this gap, and explore the potentialities and advantages of delivering compassion via the internet to promote personal resources and well-being beyond geographical barriers. According to *the Mental Capital and Wellbeing: Making the most of ourselves in the 21st century* project, it is expected that achieving small changes in overall well-being levels of the general population would consequently lead to higher decreases in percentages of mental health illness and subclinical disorders [27]. Thus, emphasizing positive psychological states, such as compassion, would act as protective factors for social, physical, and mental health. Specifically, Neff and Costigan [28] pointed out that treating oneself with care and compassion is a powerful way to enhance intrapersonal and interpersonal well-being.

In this regard, although the ABCT protocol was developed to be applied in Spanish speakers, there are no data available on its effects on the well-being outcomes of this population or on whether it could be delivered in a feasible way through the internet. Therefore, there is a need to continue exploring ways of approaching the general population with these effective resources, which is one of the main advantages of delivering self-applied interventions over the internet.

### Aims and Hypotheses

The main aim of this study is (1) to investigate the feasibility of the Internet Attachment–Based Compassion Therapy (iABCT), a web-based version of ABCT, in the general population. Additional objectives are (2) to analyze the preliminary effects of iABCT on happiness, compassion, self-compassion, dispositional mindfulness, general health, purpose in life, nonattachment, attachment styles, self-criticism, and positive and negative affects at postintervention and 3-month follow-up; (3) to explore cost-effectiveness by means of changes in overall health status levels; (4) to investigate the mechanisms of change, predictors, and associations between outcomes; and (5) to assess adverse or unwanted effects and facilitators and barriers to the intervention received.

The principal hypothesis is that iABCT will be feasible and well accepted by participants in terms of attrition, expectations, satisfaction, usability, and opinion. Second, iABCT will show efficacy in promoting significant changes with moderate-to-large within-group effect sizes in self-reported measures of happiness, compassion, self-compassion, dispositional mindfulness, self-criticizing, nonattachment, purpose in life, attachment, and overall health status. We also hypothesize that gains will be maintained at 3-month follow-ups. Third, changes in overall health levels will demonstrate the cost-effectiveness of iABCT. Fourth, significant associations will be found between changes in compassion, self-compassion, dispositional mindfulness, general health, purpose in life, nonattachment, attachment styles, self-criticism, positive and negative affects, and happiness. Specifically, improvements in happiness scores and overall health status will be predicted by self-reported self-compassion. Increments in secure attachment style would mediate the relationship between self-compassion and happiness. Finally, low rates of adverse or unwanted effects are expected.

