### Outcome Measures

Participants will be assessed at baseline (preintervention), postintervention, and 3-month follow-up after they complete the intervention. Assessments will be conducted online via the website [36], where the iABCT will be hosted, and via a telephone interview at pre- and postintervention, except for the 3-month follow-up that will be conducted only via the website. Both participants and researchers will receive email reminders of each assessment time. The study variables and assessment times are summarized in Table 2.

**Table 2 table2:** Study measures, time of assessment, and source of measurement.

Measures	Aim	Assessment point	Assessment source
Admission interview	Screen eligibility criteria (inclusion/exclusion)	Pre^a^	Phone interview
Sociodemographic data	Sex, age, educational level, occupation, and civil status	Pre	Phone interview
M.I.N.I. 7.0.2.^b^	Psychological diagnosis (exclusion criterion)	Pre	Phone interview
Meditation data	Source of learning, frequency, duration of each session (in minutes), lifetime practice (in years), and context of practice	Pre	Phone interview
PHI^c^	Well-being	Pre, post^d^, and FW^e^	Web
SCS-26^f^	Self-compassion	Pre, post, and FW	Web
Compassion scale	Compassion	Pre, post, and FW	Web
FSCRS-SF^g^	Two forms of self-criticism: inadequate self and hated self and the ability to self-reassure	Pre, post, and FW	Web
FFMQ-15^h^	Dispositional mindfulness and mindfulness facets	Pre, post, and FW	Web
RQ^i^	Attachment styles	Pre, post, and FW	Web
GHQ-12^j^	Mental health recent symptoms, feelings, or behaviors	Pre, post, and FW	Web
NAS-7^k^	Nonattachment	Pre, post, and FW	Web
I-PANAS-10-SF^l^	Positive and negative affects	Pre, between modules, post, and FW	Web
PIL-10^m^	General sense of meaning and purpose in life	Pre, post, and FW	Web
Compassion Practice Quality Questionnaire	Difficulties related to the practice of compassion meditation	Between modules, post, and FW	Web
Expectations and Satisfaction Questionnaires	Participants’ expectations before the intervention and their satisfaction after it	Pre and post	Web
UAQ^n^	Usability and acceptability of the internet-based intervention	Post	Web
Qualitative opinion interview	Opinions on the internet intervention, the modules, and unwanted or unexpected effects	Post	Phone call
Attrition rate	Percentage of participants that drop out of the intervention after accessing it for the first time	Post	Web

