### Psychological and Mental Health Outcomes

The primary outcome is well-being, which will be assessed using the *Pemberton Happiness Index* [42].

Secondary outcomes include the following: the *Compassion Scale* [43] and the *Self-Compassion Scale* [44] will be used to assess compassion and self-compassion, respectively. Self-criticism will be measured using the *Forms of Self-Criticizing/Attacking and Self-Reassuring Scale-Short form* [45]. Dispositional mindfulness will be assessed using the short *Five Facets of Mindfulness Questionnaire* [46]. The *Relationships Questionnaire* [47,48] will be used to assess attachment styles (ie, secure, preoccupied, dismissive, and fearful). The *General Health Questionnaire* (GHQ-12) [49,50] will be included to measure general mental health status. Nonattachment (eg, I can let go of regrets and feelings of dissatisfaction about the past when pleasant experiences end, I am fine moving on to what comes next) will be assessed using the *Non-Attachment Scale* [51], and positive and negative affects will be measured using the International Positive and Negative Affect Schedule Short Form [52]. The *Purpose-In-Life Test* [53] will assess the general sense of meaning and purpose in life. Difficulties related to the practice of compassion meditation will be assessed using the *Compassion Practice Quality Questionnaire* (adapted from Del Re et al [54]) that has been specifically developed for this study, which includes 10 items that participants score on a scale ranging between 0 and 100, indicating the percentage of the time that their experience reflects each statement.

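### Attrition, the first-named domain of the feasibility hypothesis, counts only dropout after first access, so allocated participants who never start are left out and loss can only be matched or understated

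*Protocol article*

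**What the plan says.** Aims and Hypotheses makes feasibility the main aim and ties the principal hypothesis to five domains, attrition first: "The principal hypothesis is that iABCT will be feasible and well accepted by participants in terms of attrition, expectations, satisfaction, usability, and opinion". Effects on happiness rank lower in the same section: "Additional objectives are (2) to analyze the preliminary effects of iABCT on happiness".

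Feasibility Outcomes treats the attrition rate as the measure of adherence. Table 2, under Outcome Measures, defines it: "Percentage of participants that drop out of the intervention after accessing it for the first time". The Statistical Analysis Plan section reports attrition and dropout as percentages, together with patterns of missing data.

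Recruitment gives the order of events. Eligible people who consent are allocated, receive an account and password by email, and complete baseline by website and telephone before the intervention begins. The programme is fully self-applied, without systematic telephone support, and must be finished within 10 weeks.

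Two further statements bear on the point. Psychological and Mental Health Outcomes says "The primary outcome is well-being", and the abstract says "The primary outcome was measured using the Pemberton Happiness Index". The abstract's conclusions say that the study will allow revision of the intervention and design, "as well as the initiation of a future randomized controlled trial".

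**The concern.** The attrition clock starts at first access to the intervention, but a participant belongs to the study from consent and allocation. Between the two lies a stage at which people can be lost. A person lost there is a feasibility loss for a self-applied web programme, yet does not enter the rate on which the principal hypothesis is first judged. The omission works in one direction only.

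Two features make it harder for a reader to put the rate in context. The only outcome called primary is a well-being index, although feasibility is the main aim. And the article gives no level of attrition at which the sponsor would judge the programme feasible or ready for a randomised trial.

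**Working it through.** **Inputs from the article.** Minimum sample 35 (Sample Size). Attrition counted only after first access (Table 2). Consent, allocation, login and baseline earlier (Recruitment). The 35 is a choice within a cited range of 24 to 50, not the output of a formula, so there is no figure of the plan's own to reproduce beyond noting that 24 ≤ 35 ≤ 50.

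**Assumed inputs.** The article gives no number of non-starters and no expected dropout. Let N be the number allocated, k those who never open the intervention, and D those who drop out after opening it. I take N = 35, D = 4 and k from 0 to 7. D = 4 gives 4/35 = 11.4%, close to 11.6%, the only dropout figure in the article; that figure comes from a cited trial of another programme and is not an assumption of this study.

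**Direction.** Loss among all allocated is (D + k)/N. Table 2 restricts the numerator to D but does not spell out the denominator, so both readings are checked.

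- Denominator of starters, D/(N − k): the shortfall is (D + k)/N − D/(N − k) = k(N − k − D)/[N(N − k)]. Since D cannot exceed N − k, this is never negative.
- Denominator of all allocated, D/N: the shortfall is k/N, also never negative.

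The reported rate therefore equals or understates the loss on either reading. The two agree when k = 0 (or, on the starters' denominator, if every starter drops out).

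**Size.**

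| Non-starters k | D/(N − k) | D/N | (D + k)/N | Exact 95% CI for (D + k)/N |
|---|---|---|---|---|
| 0 | 4/35 = 11.4% | 11.4% | 4/35 = 11.4% | 3.2% to 26.7% |
| 2 | 4/33 = 12.1% | 11.4% | 6/35 = 17.1% | 6.6% to 33.6% |
| 4 | 4/31 = 12.9% | 11.4% | 8/35 = 22.9% | 10.4% to 40.1% |
| 7 | 4/28 = 14.3% | 11.4% | 11/35 = 31.4% | 16.9% to 49.3% |

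Check of the last row: 7 × (35 − 7 − 4)/(35 × 28) = 168/980 = 17.1 percentage points, which is 31.4% − 14.3%.

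A second assumed case has heavier later dropout: 5 non-starters, and 9 of the 30 starters leave. The starters-only rate is 9/30 = 30%; loss among those allocated is 14/35 = 40% (Wilson 95% CI 26% to 56%).

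**Whether a criterion is workable at 35.** As an illustration only, a rule to proceed if at most 10 of 35 are lost passes with binomial probability 0.925 if true attrition is 20%, 0.51 if 30%, 0.112 if 40% and 0.008 if 50%. A rule of this kind separates 20% from 40% reasonably well, but at 30% it is close to a coin toss.

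**The case against.** The strongest reply is that non-starters are not lost from view. Table 2 logs each participant's use, including entries to modules; the Statistical Analysis Plan section reports missing-data patterns and includes an intention-to-treat analysis; Recruitment has the team contact people who withdraw and ask for reasons. So the full loss can be recovered from planned data. That stands, and it makes the repair cheap. But none of these provisions redefines attrition or counts non-starters in it.

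It can also be said that people who volunteer, pass a diagnostic interview and complete a baseline are likely to start, so k may be small. That is possible; the article offers no figure either way. Nor does doing baseline on the same website close the gap, because Table 2 refers to access to the intervention.

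Some stronger readings are tempting but not supported.

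- A reader might infer that happiness has displaced feasibility as the study's main question. The index is named under a psychological-outcomes heading, feasibility outcomes have their own section, and the sample size is not based on the index. This is mainly a labelling matter, although the abstract's wording carries no such limit.
- A reader might infer that the hypothesis cannot fail, or that the study cannot answer its main question. Without a threshold there is no prespecified pass or fail test in the article. A descriptive mixed-methods report can still investigate feasibility and can still look poor.
- A reader might take the abstract as a commitment to a randomised trial. It says the study will allow one, after revision and fine-tuning.
- A reader might infer that the attrition rate will set the dropout allowance of that trial. Sample Size lists means, standard deviations, effect size and confidence intervals as the parameters for powering it and does not mention attrition.

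**Conclusion.** The point holds for the definition of attrition. As written, Table 2 leaves out allocated participants who never open the programme, so the rate can equal the loss among those allocated or understate it, never overstate it. The direction follows from the text and simple algebra. The size does not: in the first illustration the gap runs from 0 to 17.1 percentage points as assumed non-starters go from 0 to 7 of 35, and in the second it is 10 points. The intervals at this sample size are wide, so a modest gap would lie within sampling error, but it would still be a bias in a known direction.

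The status of the well-being index needs one clarifying statement. The lack of a stated criterion means that the judgement of feasible would be made without a prespecified test, which is worth repairing but does not invalidate the study. Overall this should be fixed; it is not a flaw that stops an uncontrolled feasibility study from being useful.

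**What to change.** 1. In Table 2 and the Statistical Analysis Plan section, define attrition over all consented and allocated participants as not completing the last module within the 10-week maximum. Count non-starters as attrition.
2. Report non-uptake (allocated, intervention never opened) and dropout after first access as separate components, and give total attrition with an exact or Wilson 95% confidence interval.
3. State that the Pemberton Happiness Index is primary only among the preliminary-effect outcomes, and that the principal hypothesis is judged on the feasibility outcomes. This avoids replacing the primary outcome after enrolment has begun.
4. Before data are analysed, let the sponsor set and justify its own attrition criterion for proceeding to the randomised trial. Cut-offs such as 10 of 35 to proceed, or 18 of 35 not to proceed unchanged, are illustrations with no basis in the article. Any rule chosen should be shown with its pass probabilities, including at intermediate rates.

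Cost: wording changes, and an update of the registry entry where it carries the same definitions. Allocation is known and module use is already logged, so no new data are needed. Reported attrition may look less favourable, and a participant still working through the modules at week 10 would count as not completing. Enrolment started in February 2020, so the change must be recorded as made after that date. The article already provides for revising the analysis plan before database lock and reporting changes, and analysis is due to start only in October 2020.

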## Methods

### Study Design

This feasibility study and open trial features a single-arm, uncontrolled, within-group design with 3 measurement points at baseline (preintervention), immediately after the intervention (postbaseline), and 3-month follow-up with an embedded qualitative and quantitative assessment. Participants will be allocated to iABCT. The study was registered under Clinicaltrials.gov (NCT03918746) and will be conducted following the extension of the Consolidated Standards of Reporting Trials (CONSORT) statement for pilot and feasibility studies [29], the Consolidated Standards of Reporting Trials of Electronic and Mobile HEalth Applications and onLine TeleHealth guidelines [30], and the Standard Protocol Items: Recommendations for Interventional Trials (SPIRIT) guidelines (Multimedia Appendix 1) [31]. The SPIRIT checklist was used as a guide for reporting this study protocol (version 1; March 6, 2019).

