### Statistical Analysis Plan

Normality and homoscedasticity data assumptions will be checked using Kolmogorov-Smirnov (K-S) and Levene tests. Significant differences on categorical variables (eg, sex, educational level, occupation, etc) will be assessed using a chi-square test. Attrition and dropout rates will be calculated by reporting percentages and patterns of missing data. The Little missing completely at random (MCAR) test will be used to assess the assumption that data are MCAR [55]. Means and SDs will be reported for all the measures at each assessment point. A preliminary efficacy analysis will be performed using means of comparison for related samples based on intention-to-treat and per-protocol analyses. Mixed model analyses for primary and secondary outcome measures will be implemented using the linear mixed-effects models (MIXED) procedure with 1 random intercept per subject. *Time* will be treated as a within-group factor, and significant effects will be followed up with pairwise comparisons (adjusted by a Bonferroni correction). Sensitivity analyses will be performed to assess the robustness of the findings in terms of different methods for handling missing data (ie, mixed models with and without imputation, maximum-likelihood estimation, and maximum-likelihood multiple imputation) [56]. Within-group effect sizes (pre vs post and pre vs 3-month follow-up) will be reported using Cohen *d* and its 95% CI. For the analyses of associations between the intervention outcomes, predictors of change, and mechanisms of actions, several statistical tests will be performed such as Pearson correlation, multiple regressions, and mediation analysis using the bootstrapping approach [57]. A cost-effectiveness and cost-utility analysis will be conducted using the GHQ-12 based on literature proposals [58,59]. The mapping technique proposed by Lindkvist and Feldman [59] will be used to predict health state utility values using a crosswalk transformation algorithm from the GHQ-12 to the health utility measure (EuroQoL–5 dimension [EQ-5D]). Spanish tariffs of EQ-5D will be used as the reference population [58,60]. Additionally, participants’ qualitative responses regarding adverse or unwanted effects and facilitators and barriers to the intervention received will be explored using a qualitative content analysis and coding and the categorizing data approach by counting the frequency of words with NVivo software (QSR International). Statistical analyses of quantitative data will be performed using SPSS version 23 for Windows (IBM Corp). The statistical analysis plan (SAP) will be revised by all the study team members before the database is locked for use in the final statistical analysis. Any discrepancies or changes made between the analysis plan in this protocol and final SAP will be explained and reported.

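### Hypothesis 3 infers cost-effectiveness from a change in health alone, but a single-arm design with no named cost data can only describe a before-after change in mapped utility

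*Protocol article*

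**What the plan says.** Three parts of the protocol article bear on this.

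- **Aims and Hypotheses.** Objective 3 is "to explore cost-effectiveness by means of changes in overall health status levels". The matching hypothesis is firmer: "Third, changes in overall health levels will demonstrate the cost-effectiveness of iABCT".
- **Statistical Analysis Plan.** "A cost-effectiveness and cost-utility analysis will be conducted using the GHQ-12 based on literature proposals". The text goes on to a "crosswalk transformation algorithm from the GHQ-12 to the health utility measure", the EQ-5D, with Spanish tariffs as reference. No cost input follows.
- **Study Design and Outcome Measures.** The study "features a single-arm, uncontrolled, within-group design with 3 measurement points". On data collection, "The study variables and assessment times are summarized in Table 2". In that table the GHQ-12 is described as covering "Mental health recent symptoms, feelings, or behaviors" and is taken at baseline, postintervention and 3-month follow-up. No row of the table, and nothing in the sections on screening, feasibility and psychological outcomes, concerns cost, resource use, service use or productivity.

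**The concern.** The hypothesis draws an economic conclusion from a health outcome. A change in health, however large, says nothing about cost-effectiveness until it is set against what it cost and against what would have happened under an alternative. The analysis section repeats the step: it is specific about how GHQ-12 scores become utilities and silent on what they are to be compared with.

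At stake is one of five stated objectives and its hypothesis. Read literally, the hypothesis would count as supported by an improvement in GHQ-12 scores from before to after the programme, with no economic evidence behind it. The study is meant to prepare a larger RCT, so the error could carry forward into that trial's rationale.

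**Working it through.** **1. Is there a figure to reproduce?** No. The article states no cost, QALY gain, cost-effectiveness ratio or threshold. The check is therefore whether the inputs exist.

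**2. Inputs needed and inputs available.** The quantity behind both planned analyses is

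ICER = (C1 − C0) / (E1 − E0),

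where 1 is iABCT and 0 is the alternative.

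| Term | In the article |
|---|---|
| E1, effect under iABCT | Available: GHQ-12 mapped to EQ-5D utility at three time points |
| E0, effect under the alternative | Not observed: single arm, no control |
| C1, cost under iABCT | No variable and no source named |
| C0, cost under the alternative | No variable and no source named; no alternative exists in the design |

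One of four terms is available. The nearest thing to resource data is the patterns-of-use row of Table 2 (programme length, time per module, number of entries). That is a feasibility outcome, carries no unit cost and is not linked to the economic analysis.

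**3. What can be estimated.** The mean of (utility after − utility before) in one group, with a confidence interval. This equals E1 − E0 only if participants' utility would have stayed exactly at baseline without iABCT, which an uncontrolled design cannot check.

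**4. Illustration only; every value below except the timings is assumed.** Let mapped utility rise linearly by u over w weeks and then hold for the 13 weeks to follow-up. The article estimates 8 weeks for the programme and allows at most 10.

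QALY gain = u × (w/2 + 13) / 52

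- u = 0.01, w = 8: 0.01 × 17/52 = 0.0033
- u = 0.03, w = 8: 0.03 × 17/52 = 0.0098
- u = 0.05, w = 10: 0.05 × 18/52 = 0.0173

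With an assumed net cost per person between 20 and 300 euro, the extremes are 20/0.0173 ≈ 1,160 and 300/0.0033 ≈ 91,800 euro per QALY (unrounded QALY gains used in the division).

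Now fix the cost at 100 euro, u = 0.03 and w = 8, and let f be the share of the gain that would have occurred without iABCT:

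ratio = 100 / [0.00981 × (1 − f)]

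| f | Euro per QALY |
|---|---|
| 0 | 10,196 |
| 50% | 20,392 |
| 90% | 101,961 |
| 100% | undefined |

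The observed health change is identical in all four rows. The trial has no data on f. These figures show only that the conclusion turns on terms the design does not supply; they are not estimates for iABCT.

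**The case against.** The case for leaving the plan alone has real substance.

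- **Costs may exist on the provider's side.** The programme is self-applied, with contact only for technical help, so its delivery cost is mainly platform, hosting and staff time. Such costs would not be expected in a table of participant measures. Nor is that table exhaustive: the knowledge check in each module and the reasons for withdrawal have no row. This stands. A reader might infer that no cost per QALY could be computed at all. The documents do not support that: a before-after ratio could be formed from outside delivery costs. It would still lack E0 and C0, so it could not show cost-effectiveness.
- **Detail may sit in the full SAP.** Perspective, unit costs and costing source are commonly left there, and their absence from an article is no finding by itself. This also stands. But no such detail could make a change in health alone demonstrate cost-effectiveness in an uncontrolled study. That inference is stated, not omitted.
- **The aim is exploratory.** Objective 3 says explore, and neither the abstract nor the Discussion makes a cost-effectiveness claim. So a reader should not infer that the team will report the programme as cost-effective; a hypothesis is an expectation, not a result. What remains is that objective and hypothesis disagree, and that even the softer objective names health change as the only means.
- **Ceiling effect.** A reader might also infer that healthy volunteers have little room for utility to rise. The article gives no baseline GHQ-12 score, mapped utility or mapping range, so this cannot be established and plays no part here.

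**Conclusion.** The point holds in a limited form. The inference in hypothesis 3 is wrong as written, and the analysis sentence commits to two economic analyses for which the article names only the effect input. The trial can deliver a before-after change in GHQ-12-mapped utility; it cannot deliver an incremental cost per incremental effect, and no ratio built from outside costs would support a conclusion on cost-effectiveness.

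This should be fixed, but it does not threaten the study. It touches one additional objective, and leaves the feasibility aims, the Pemberton Happiness Index as primary outcome and the minimum of 35 participants untouched. No trial-based size can be put on the error, because the article gives no economic figures; the per-QALY numbers above rest wholly on assumed costs and utility gains. The verdict does not depend on them. It rests on the single-arm design and on the wording of the hypothesis, both of which are explicit, and on the article naming no cost variable or source.

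**What to change.** Change wording in three places.

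1. Delete hypothesis 3.
2. Reword objective 3, for example: *to describe the mean change in GHQ-12-mapped EQ-5D utility from baseline to postintervention and to 3-month follow-up, with 95% CI*.
3. Replace the cost-effectiveness and cost-utility sentence in the Statistical Analysis Plan with the same descriptive analysis. Keep the mapping and the Spanish tariffs, and add that no inference on cost-effectiveness will be drawn and that the question is left to the future RCT.

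If delivery costs are logged (hosting, screening-call time, technical-assistance contacts), report them descriptively to plan the costing of that RCT, not as a ratio to the utility change.

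The cost is editorial: no new measure, visit or participant is needed, and logging is optional. The trial gives up a claim its data could not support.
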